### Study design and research setting

The RECALL study combines a multicenter, prospective cohort study on older patients with depression who are referred for ECT to study the broad palette of cognitive side-effects (and their determinants), with an embedded cross-over trial to examine rivastigmine as a treatment option for patients with inter-ictal delirium (see Figure 1 for a schematic overview of the RECALL study). The trial is designed as a randomized, double blind, placebo-controlled, cross-over trial. Patients are recruited at four mental healthcare institutes; (1) GGZ inGeest (partner-institution of Amsterdam University Medical Center, formerly VU University Medical Center), Amsterdam, The Netherlands, (2) Parnassia Psychiatric Institute, The Hague, The Netherlands, (3) OLVG-West, Amsterdam, The Netherlands, and (4) UPC KU Leuven, Leuven, Belgium. GGZ InGeest, and Parnassia Psychiatric Institute are general mental healthcare institutes; OLVG West is a general hospital with a psychiatric ward, and UPC KU Leuven is an academic hospital.

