### Exclusion criteria

Exclusion criteria for participation in the cohort study are comorbid somatic conditions that are a relative contraindication for ECT, according to the prevailing Dutch ECT-guidelines, e.g., recent (within 3 months) myocardial infarction or cerebrovascular accident, a diagnosis of neurocognitive disorder, insufficient command of the Dutch language and prior participation in the cohort study (27). Additional exclusion criteria for participation in the trial are: diagnosed (treatable) somatic causes of delirium other than ECT (e.g., urinary tract infection) and contra-indications for rivastigmine use, such as bradycardia or atrio-ventricular (AV) conduction disorder (first degree AV-block excluded), current use of a AChI or a known allergic or adverse reaction to rivastigmine. As it is a cross-over trial, each cross-over patient serves as his or her own control. Since large, intercurrent changes in individual patients' situation hamper a cross-over comparison, patients who switch from (right) unilateral electrode placement (RUL) to bilateral electrode placement (BL), or individuals who receive dose adjustments of antipsychotics during the trial will be marked as drop-outs. Notably, participation in the cohort can be continued when patients drop out due to trial specific exclusion criteria.

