### RECALL trial: Treatment allocation, intervention, and blinding

After inclusion in the trial, randomization is organized with a two by two Williams design (29). Block randomization is performed by the pharmacy department of the Amsterdam University Medical Center—location VUmc, with stratification for each site. Patients are randomly assigned to either the rivastigmine-followed-by-placebo group, or the placebo-followed-by-rivastigmine group. Each treatment arm lasts for four consecutive ECT sessions (Figure 1). Except for the unblinded nurse or research assistant (i.e., nurse or research assistant who is not involved in other parts of the study, nor in clinical practice, but only applies the patches), all other study members are blinded. “Trial treatment randomization lists” with codes are provided by an independent pharmacist and will only be available for the unblinded nurse or research assistant who applies the patches. Rivastigmine patches delivering 4.6 mg/24 h (Hexal AG, Holzkirchen, Germany) and Hansaplast® placebo patches (of similar size) are labeled in accordance with EU GMP annex 13 regulations and supplied to the sites. To improve and monitor adherence to the trial protocol, drug accountability lists are filled in. The Tmax of rivastigmine patches is 10–16 h, therefore the application of the rivastigmine (and placebo) patches is done the evening prior to ECT. The patch is removed after 24 h. As previously mentioned, during the trial, co-medication is allowed and there are no restrictions to clinical care as usual. As specified in the exclusion criteria however, patients with adjustments in antipsychotic medication or in electrode placement, are excluded from the trial. Benzodiazepines are allowed (e.g., in cases of profound agitation or insomnia). All changes in medications during the trial are registered after every ECT-session. Prior to each ECT-session, side-effects of rivastigmine are assessed, and in case of serious side-effects (e.g., gastrointestinal adverse reactions such as severe nausea), the participation in the trial will be stopped and rivastigmine discontinued. In case of persistent side-effect after discontinuation, the clinician will treat the patient according to the clinical picture (e.g., anti-emetics in case of nausea).

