#### Primary outcome measure

During the trial, the effect of rivastigmine on inter-ictal delirium is examined through the Delirium Rating Scale-Revised-98 (DRS-R-98) (30). It was demonstrated that the DRS-R-98 is sensitive, specific, reliable, and easy to use for the assessment of severity of a delirium (30). We will compare delta-scores of the DRS-R-98 computed over the period of rivastigmine-use and placebo (T3-T0 and T6-T3, depending on whether the patients start with rivastigmine or placebo). This is assessed by a trained, blinded research nurse once weekly.

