### Sample size calculation

We estimated that in our vulnerable study population, prevalence rates of delirium and profound cognitive decline are ~20%, based on a previous study (11). In order to detect a reduction on the DRS-R-98 of 4 points (SD ± 7), at 80% power with α = 0.05, 120 delirious patients should be included in a non-cross-over trial. These patients (*n* = 120) should be identified during regular ECT (cohort study). Since the estimated prevalence of inter-ictal delirium is ~20%, the cohort should include in total at least 600–1,000 persons in order to select 120 patients. This is not possible, due to limited availability of resources. Therefore, a cross-over design will be used. A cross-over design requires fewer patients than a non-cross-over trial to achieve similar power. With an estimated correlation between intra-individual measurements of *r* = 0.50, a cross-over trial requires only 25% of the number of patients (70). Hence, a total of 30 patients provide sufficient power for the trial. With an estimated dropout of 20%, 38 patients need to be included to obtain sufficient power for the trial. We aimed at a probability of 75% to include 38 delirious patients in the trial, which would amount to 210 patients in the cohort. Eventually, with an additional 20% margin of safety due to estimated prevalence, we decided to set the inclusion goal at 250 patients for the cohort, to achieve a sample of 30 delirious patients completing the trial. However, during the first months of data-collection, the prevalence of inter-ictal delirium was noticeably higher, namely ~25%. Hence, in an amendment, the goal of inclusion in the cohort was set back to 150 patients.

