#### Data analysis

Significance will be set at *p* < 0.05 for all statistics and 95% confidence intervals will be presented. Intention to treat analyses will be conducted. Descriptive baseline statistics will be generated for the patients included in the trial. As the trial is a patient cross-over design, no comparison or correction for baseline variables will be done.

To estimate the efficacy of rivastigmine on inter-ictal delirium in the RECALL trial, delta scores of the DRS-R-98 will be used. These delta scores will be computed over the period of rivastigmine (intervention, 2 ECT sessions, 7 days) and placebo (comparison, 2 ECT sessions, 7 days) separately. For further details, see section Primary outcome measure. Analysis of Variance (ANOVA) by a mixed model for repeated measures, with treatment (rivastigmine vs. placebo) as a within effect and sequence of treatment (arm A vs. arm B) as a between factor, will be performed. Additionally, the association between rivastigmine and (delta-scores of the) DRS-R-98 will be examined in a traditional regression model, with putative effect modifiers, confounders and determinants.

Cox's regression analyses will be conducted in the RECALL cohort, with outcome defined as the (time to) occurrence of inter-ictal delirium measured by a positive CAM and/or a decline of MMSE of 4 points, adjusted for putative effect modifiers, confounders and determinants. Additionally, putative patterns of cognitive decline will be identified by data-driven methods (e.g., latent-class analysis), based on cognitive outcome measures. Future analyses in the data will depend on appropriate research questions.

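### Sequence is randomised within site, but the stated primary model has no place for a site difference in the period-to-period change; if there is one, the confidence interval is conservative

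*Protocol article*

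**What the plan says.** Under Study design and research setting: "Patients are recruited at four mental healthcare institutes". Under RECALL trial: Treatment allocation, intervention, and blinding, sequence is block-randomised "with stratification for each site".

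The primary outcome is one DRS-R-98 delta score per period, "T3-T0 and T6-T3, depending on whether the patients start with rivastigmine or placebo" (Primary outcome measure). Under Data analysis, the primary analysis is a mixed-model ANOVA "with treatment (rivastigmine vs. placebo) as a within effect and sequence of treatment (arm A vs. arm B) as a between factor". Neither site nor period is named. The same section says that, because the design is a cross-over, "no comparison or correction for baseline variables will be done". It then adds a further analysis of the delta scores "in a traditional regression model, with putative effect modifiers, confounders and determinants", without listing the covariates.

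**The concern.** Stratifying by site makes the two sequences nearly equal in number within each site. A site difference in how scores move from the first period to the second therefore contributes little to the true sampling error of the treatment estimate. A model that does not know the site still counts that difference as residual noise, so its standard error is too large and its test is conservative.

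The reason given for making no correction is, in the words of the Exclusion criteria section, that "each cross-over patient serves as his or her own control". This deals with whatever is the same in both delta scores, but not with a site difference between them. The assessment schedule shows how one could arise. The within-patient contrast is (T3 - T0) - (T6 - T3) = 2×T3 - T0 - T6. In Table 1, T0 is the day before the first trial ECT, while T3 and T6 are the day after the second and fourth. If a site's device or technique shifts its post-ECT scores by s points relative to T0, the contrast shifts by 2s - s = s. This is a possible mechanism only; the article reports no such shift.

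At stake is precision in a trial planned for about 30 completers. Bias is not at issue.

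**Working it through.** **Inputs from the article (Sample size calculation).** Effect 4 points, SD 7, within-patient correlation 0.50, 30 completers. The article's 30 follows from its own 120: 120 × (1 - 0.5)/2 = 30. (The 120 does not follow from the stated effect, SD, power and alpha, which give 49 per arm or 98 in total by the normal approximation. That is a separate matter and is not used here.)

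**Assumptions.** SD 7 and r = 0.50 apply to the delta scores; completers per site are 10, 8, 6 and 6; sequence is exactly balanced within site; the test is two-sided at 5%. The site-by-period SD, g, is not in the documents and is varied from 0 to 4 points.

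**Step 1: base case.** SD of the period difference = 7 × √(2 × (1 - 0.5)) = 7. Regressing the period-1 minus period-2 difference on sequence coded ±1 gives SE = 7/√30 = 1.278. With 28 df, t = 2.048 and the half-width is 2.618; power is 85.6%. This base model includes an overall period effect as its intercept, which is generous to the plan, since the article names no period term.

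**Step 2: site main effect.** In random-intercept models on simulated trials (40 per setting), adding site left the treatment estimate identical to machine precision and the mean SE unchanged: 1.296 v 1.296 at a between-site SD of 3, and 1.266 v 1.266 at an SD of 10. The main effect is not the issue.

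**Step 3: site-by-period, expected size.** Without site, the expected residual mean square is 49 + c × g², where c = (30 - Σn²/30)/28. Here Σn² = 100 + 64 + 36 + 36 = 236, so c = (30 - 7.867)/28 = 0.790. With site in the model the mean square is 49 on 25 df (t = 2.060) and the half-width is 2.632.

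| g | mean square without site | half-width without | half-width with | without v with |
|---|---|---|---|---|
| 0 | 49.00 | 2.618 | 2.632 | -0.5% |
| 2 | 52.16 | 2.701 | 2.632 | +2.6% |
| 3 | 56.11 | 2.802 | 2.632 | +6.4% |
| 4 | 61.65 | 2.936 | 2.632 | +11.6% |

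Break-even: 49 + 0.790 × g² = 49 × (2.0595/2.0484)², so g² = 0.676 and g = 0.82.

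**Step 4: simulation (4,000 trials per setting).** Mean half-width without v with site: 2.675 v 2.602 (g = 2), 2.781 v 2.608 (g = 3), 2.901 v 2.606 (g = 4), i.e. +3%, +7% and +11%. Coverage without site was 95.6%, 96.2% and 97.0%; with site, about 95%. The mean estimate was between -4.00 and -4.03 for a true -4.

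**Step 5: total SD held at 7.** If the planning SD already contains the site variation, the residual variance is 49 - g². The excess width without site is then +2.9%, +7.9% and +17.0% for g = 2, 3 and 4. For example, at g = 4 the mean squares are 33 + 12.65 = 45.65 v 33, and √(45.65/33) × 2.048/2.060 = 1.170. In a check of 6,000 simulated trials per setting, power without site was 86%, 89% and 91%, against 87.5%, 92% and 95% with it.

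**The case against.** The strongest reply is that nothing in the article states or sizes a site-by-period difference. Device and type of institution differ between sites but stay the same across a patient's two periods. The 1-to-2-day screening lag belongs to the weekly cohort screening and is not said to vary by site, and the Table 1 footnote fixes one measurement day for all. If there is no such difference, the added terms make the interval slightly wider. The stated analysis is valid either way, and an analysis plan that is not shown may deal with site. All of this stands, and it makes the point conditional and modest. It does not remove the point: the article writes out the terms of its primary model, and the stratification factor is not among them. The additional regression does not put site into the primary test.

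Four stronger readings are tempting and are not supported:

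- **That the plan forbids all correction.** The sentence is limited to baseline variables, and an adjusted regression follows it. Site is neither named nor excluded.
- **That the interval is too wide as a matter of fact.** It is so only if g exceeds about 0.8 points.
- **That power falls below the planned 80%.** Falls to 79% or 76% appear only if a site-by-period SD of 4 or 5 is added on top of the planned SD of 7. With the total held at 7, power without site is 86% or more.
- **That the cohort Cox model needs the same change.** This would rest on screening lag being set by site, which the article does not say.

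**Conclusion.** The point holds in conditional form. The primary model as stated does not carry the randomisation stratum in the only place where it could matter, the period difference. The treatment estimate is unbiased regardless. Omitting the term makes the interval about 0.5% narrower if sites do not differ, and about 3%, 6 to 7% or 11% wider at an assumed site-by-period SD of 2, 3 or 4 points. The excess does not depend on adding variance to the planning SD: it is as large or larger when the total SD is held at 7. These figures rest on the assumed site sizes, on near-exact balance within site, and on SD 7 and r = 0.50 applying to the delta scores. The consequence is lost precision and a conservative test, not a wrong conclusion. It is worth correcting because the possible gain far exceeds the cost.

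**What to change.** Before unblinding, state that the primary analysis takes each patient's period-1 minus period-2 difference in DRS-R-98 delta score and fits it by sequence and site. For patients with both periods, this is equivalent to including period, site and site-by-period in the mixed model; it also supplies the period term that the stated model does not name. Adding site as a main effect only would not do.

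Limit the sentence on baseline correction so that it clearly does not exclude site, the randomisation stratum.

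Cost: wording only, and three degrees of freedom (28 to 25). If sites do not differ, the interval is about 0.5% wider (2.060/2.048 = 1.005) and power moves from 85.6% to 85.3%. No extra patients or data are needed.

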### Monitoring, auditing, and harms

#### Monitoring and auditing

A data monitoring committee has been installed, consisting of the Clinical Research Bureau (CRB) of VUmc, Amsterdam (currently Amsterdam University Medical Center). This CRB is independent from the sponsor and has no competing interests. In summary, the CRB monitors whether the rights and well-being of the respondents are protected; whether data from the research is reported correctly and fully verifiable in source documents; and whether the execution of the study is in accordance with the protocol or amendment(s) approved at that time, with Good Clinical Practice (GCP) and with the relevant legal requirements. In addition, monitoring visits at all Dutch sites are conducted shortly after the start of the study, and once yearly during the study. Audits on trial conduct are performed at random by the Amsterdam Public Health Research Institute. Considering the low risk of rivastigmine, as a long-term registered drug, an additional Data and Safety Monitoring Board was not installed. Likewise, interim analyses will not be conducted. Notably, all documents, including Patients' Information Folder (PIF) and Patients' Informed Consent forms (IC), and protocols for MRI and EEG measurements, blood and urine collection, laboratory evaluation and storage and data management plan (including information on data entry, coding, security and storage) are available upon request.

#### Harms

Adverse events are defined as 'any undesirable experience occurring to a subject during a clinical trial, whether or not considered related to the intervention'. Therefore, we decided to note only adverse events in the trial, and not during regular ECT-treatment (cohort-study). All adverse events reported spontaneously by the subject or observed by the investigator or his staff are recorded. All serious adverse events, defined by the Central Committee on Research involving Human Subjects (CCMO), that occur in any of the participating centers are reported immediately to the principal investigator, who will report to the medical ethical board of the VUmc. The local investigators at each collaborating center are responsible for immediate reporting to the principal investigator.

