### Outcome measures

Table 1 shows a full summary of patient characteristics and outcome measures, including the time of collection.

**Table 1 T1:** Collection of patient characteristics and outcome measures in the RECALL trial and cohort.

	**Baseline**	**Regular care**		**Trial**							**Regular care in cohort**		
		**in cohort**									**after finishing the trial**		
	**Baseline**	**Max 90 minutes after ECT**	**Once a week during ECT** ^∧^	**Day before first ECT**	**Max 90 minutes after first ECT**	**Max 90 minutes after 2**^nd^ **ECT**	**Day after 2**^nd^ **ECT**^∧^	**Max 90 minutes after 3**^rd^ **ECT**	**Max 90 minutes after 4**^th^ **ECT**	**Day after 4**^th^ **ECT**^∧^	**Max 90 minutes after ECT**	**Once a week during ECT** ^∧^	**1 week after stop ECT**
Time	Ta	Tb		T0	T1	T2	T3	T4	T5	T6	Tb		
Socio-demographics	X												
*General clinical-demographics*													
Medical history	X												
Substance use	X												
Medication use	X	X		X	X	X		X	X	X	X		X
ATHF	X												
BMI	X												
Waist circumference	X												
Blood pressure	X												
*Physical activity and frailty*													
Frailty index	X												X
SPPB	X												X
Physical activity*	X												
Vision and hearing ability	X												
*Depression related clinical characteristics*													
BAI^a^	X												
GDS^a^	X												
AES^a^	X			X			X			X			X
MADRS^a^	X		X				X			X		X	X
CORE	X		X				X			X		X	X
*Neurocognitive characteristics*													
Battery of neuropsychological tests**	X												X
Self reported cognitive decline	X												X
IQCODE	X												X
(f)MRI	X												
EEG	X												
*Laboratory characteristics*													
Blood / urine sample	X			X									X
*Primary outcome measure*													
DRS-R-98				X	X	X	X	X	X	X			
*Secondary outcome measures*													
MMSE	X		X				X			X		X	X
Letter fluency	X			X			X			X			X
Clock Drawing Test	X			X			X			X			X
Reorientation time		X			X	X		X	X		X		
RASS		X			X	X		X	X		X		
CAM		X	X										
ECT characteristics		X			X	X		X	X		X		
Rivastigmine side-effects				X	X	X		X	X	X			

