
Furthermore, in order to investigate the safety and effect of rivastigmine on ECT-parameters and anesthesia, we measure blood pressure, peak heart rate, seizure length (EEG and motor duration in seconds), postictal suppression index (in %) and seizure threshold. Apart from the postictal suppression index and seizure length measured by the Thymatron IV (unavailable at sites with the spECTrum), all variables are recorded by a blinded anesthesiologist. Next, side-effects of rivastigmine are evaluated twice weekly (by a research assistant) using a four-point side-effects scale with the five most common side-effects of rivastigmine (nausea, vomiting, diarrhea, abdominal pain, allergic skin reaction), and an open question for additional side-effects.

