The cross-over design is chosen for three specific reasons; (1) to reduce the influence of confounding covariates, as each crossover patient serves as his or her own control; (2) to enable all trial patients to benefit from the study medication; and (3) most important, feasibility, as cross-over designs require fewer patients than non-cross-over designs to achieve sufficient power (71). The feasibility was the major argument for the design team as this is a population that is particularly hard to study. It is difficult to include patients due to less motivation which is a symptom of their disease, and—in case of legal incapability- doubts from the legal representative (e.g., family) to agree to an additional extensive battery of tests during the treatment. In addition, as in all studies on depression, we predict that the anhedonia and indecisiveness, core symptoms of depression, cause difficulties for patients to stay motivated during the entire study, resulting in missing data. The cross-over design allows this study to achieve sufficient power with 30 delirious patients completing the trial. A potential bias in cross-over designs may be “carry-over” effects. However, rivastigmine has a short elimination time [T1/2 patch = 3.4 h (72)], therefore a minimal “wash-out” period of 1 day is deemed sufficient. After removal of the patch, rivastigmine is eliminated for more than 99% within 24 h—or before the next ECT session is done. Furthermore, transdermal rivastigmine was chosen over other AChI due to reported superiority on gastro-intestinal side-effects and similar expected efficacy (73–75).

A limitation of our study is the possibly invalid use of the MMSE as an inclusion measure for patients with an inter-ictal delirium. It might be improper, as it is previously not validated as a tool for the diagnosis of inter-ictal delirium, or any other delirium (76). The same goes for the MMSE as a measure of delirium severity. However, we claim, based on our clinical experience, that inter-ictal delirium does not always behave as a “regular” delirium and therefore does not always meet the criteria for delirium as measured with the CAM. For example, hallucinations are often lacking, and the patients usually suffer from clouding of consciousness, persistent disorientation or reduced speed of processing. Hence, by screening for inter-ictal delirium using the CAM only, eligible patients for the trial might be missed.

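### Adverse-event recording ends with the trial, leaving about a day of recorded time after rivastigmine in one sequence and about a week in the other, so late non-serious reactions can be lost

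*Protocol article*

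**What the plan says.** The Harms section of the protocol article defines an adverse event as "any undesirable experience occurring to a subject during a clinical trial, whether or not considered related to the intervention". From this it draws the rule "Therefore, we decided to note only adverse events in the trial, and not during regular ECT-treatment (cohort-study". During the trial, spontaneous reports and staff observations are recorded. Serious events have their own sentence: those "that occur in any of the participating centers are reported immediately to the principal investigator", with no stated limit to the trial.

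Under Secondary outcome measures, "side-effects of rivastigmine are evaluated twice weekly (by a research assistant", on a four-point scale covering five listed effects (one is an allergic skin reaction) plus an open question. In Table 1 the row "Rivastigmine side-effects" is marked at T0, T1, T2, T4, T5 and T6. It is blank at T3 and in all three columns for the cohort after the trial.

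The section on treatment allocation ends trial participation for a patient with serious side-effects and then says: "In case of persistent side-effect after discontinuation, the clinician will treat the patient according to the clinical picture". Exclusion criteria adds that "participation in the cohort can be continued when patients drop out due to trial specific exclusion criteria". On drug clearance, the Discussion says: "After removal of the patch, rivastigmine is eliminated for more than 99% within 24 h".

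**The concern.** Side-effects of rivastigmine are a stated aim and a secondary outcome of the trial, so it matters how long patients are observed after exposure. The definition of an adverse event does not justify the rule drawn from it. A definition that ignores relatedness gives no reason to stop recording in a patient who has just worn the active patch and returns to the cohort.

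In a two-period cross-over, a recording window that closes with the second period gives the two sequences unequal time after active treatment. The patients with the poorest tolerance leave the trial early and pass into the part of the study where non-serious events are, by decision, not noted. The description of tolerability is at stake. The primary DRS-R-98 comparison is not affected.

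**Working it through.** **1. The plan's own figure.** The Discussion gives a half-life of 3.4 h after the patch. First-order elimination at 24 h is 1 − 0.5^(24/3.4) = 0.9925. The stated figure of more than 99% reproduces.

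**2. Placebo-first patients.** The patch goes on the evening before ECT and comes off 24 h later, so the last active patch comes off on the evening of the fourth trial ECT. T6 is the next day. Assumed clock times: removal at 20:00, visit between 10:00 and 16:00.
- Recorded time: 4 + 10 = 14 h to 4 + 16 = 20 h.
- Drug remaining: 0.5^(14/3.4) = 5.8% to 0.5^(20/3.4) = 1.7%.
- If the two-day maximum given for cohort screening (Study population and inclusion criteria) also applies to T6: 14 + 24 = 38 h to 20 + 24 = 44 h.

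**3. Rivastigmine-first patients.** Data analysis gives 7 days and two ECT sessions per period, and Table 1 agrees on the sessions. The last active patch therefore comes off a week earlier.
- Recorded time to T6: 14 + 168 = 182 h to 20 + 168 = 188 h, or 7.6 to 7.8 days. From T3 onward this is the placebo period.
- Scheduled ratings: T2 is within 90 minutes after the second ECT, with the active patch still on. T3, the first visit after its removal, has no rating. T4 is within 90 minutes after the third ECT, with a placebo patch on since the evening before.
- The allocation section instead places the check before each ECT. A check on the morning of the third ECT would also be under placebo.

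**4. The conflicting period length.** The allocation section gives four ECT sessions per treatment arm. At two sessions a week that is 14 days, and step 3 becomes 14 + 336 = 350 h to 20 + 336 = 356 h. Step 2 does not change if the last visit still follows the last ECT by a day. The imbalance does not depend on the two-session reading, but its size does.

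**5. Stopped patients.** The allocation section foresees side-effects that outlast the patch and provides clinical treatment for them. A known adverse reaction to rivastigmine is one of the trial-specific exclusion criteria, so such a patient may continue in the cohort. The Harms section does not note adverse events there. Taken together, no recording of a persisting non-serious event is stated.

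**6. What the shorter window costs.** Assume the 30 planned completers split evenly, 15 per sequence. If no late reaction is seen among n patients observed long enough, the one-sided 95% upper limit for its rate is 1 − 0.05^(1/n).
- n = 15 (rivastigmine-first only): 18.1%.
- n = 30 (both sequences): 9.5%.

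**The case against.** The strongest reply is that little drug is left to cause harm. T6 follows patch removal, and over 94% is eliminated by then under the clock times above. Dosing is also intermittent: days of observation follow the first active patch of each period, so a reaction delayed by a few days from that patch can still be recorded in the rivastigmine period. This stands. The gap concerns reactions that first appear after the last patch, or that persist.

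For stopped patients, the reaction that caused the stop is itself a trial adverse event, and serious events are not expressly limited to the trial. Medication use is still recorded in the cohort, so treatment of a lasting effect may be visible. This stands too: what may be lost is the duration of non-serious events, or their later onset. At T3 a research nurse sees the patient and spontaneous reports are recorded, so only the structured rating is missing there.

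A reader might infer that late reactions would be counted against placebo and that the safety comparison is biased towards rivastigmine. The documents do not support that. No section assigns an event to the period in which it is recorded, and Data analysis describes no within-patient safety test. Onset dates and attribution rules may be in the full protocol or the SAP, which are not shown.

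It can also be said that a condensed article leaves follow-up to resolution to the full protocol. That is fair for the missing detail. It does not answer an explicit decision to stop recording, or a schedule that shows where the ratings end.

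**Conclusion.** The point holds as a limitation of the recording window. On the two-session reading, scheduled recording after the last active patch lasts about one day in placebo-first patients and about a week in rivastigmine-first patients, whose first scheduled rating in that week is under placebo. No recording of non-serious events is stated after T6 or after a stop for side-effects.

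Delayed or persisting non-serious reactions, such as the allergic skin reaction on the protocol's own list, can therefore be missed or first appear in the record during the placebo period. The number of events cannot be estimated, because the documents give no rate. The hours rest on assumed clock times, on T6 being the last trial visit, and on a period length that the article states in two ways.

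It would go too far to say that patients stopped for side-effects are not followed: they receive clinical care and may stay in the cohort. What is absent is a stated recording. This is a modest, easily corrected weakness in a secondary objective.

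**What to change.** 1. In Table 1, add the rivastigmine side-effect rating at T3.
2. In Harms and Table 1, record adverse events and the five-item scale once more at the next weekly cohort visit, or at the visit one week after ECT ends, for every randomised patient, including those stopped early. For a placebo-first patient, a weekly visit 7 days after T6 extends the window to 14 + 168 = 182 h to 20 + 168 = 188 h, matching the other sequence.
3. Report events by onset relative to the last rivastigmine patch as well as by period.
4. Reconcile the two statements of ECT sessions per arm, and the two timings of the side-effect check (before ECT in the allocation section, after ECT in Table 1).

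The cost is a few minutes at visits that already take place (MMSE, MADRS and CORE are done weekly in the cohort after the trial) and one extra table. There are two drawbacks. The Discussion expects motivation problems and missing data in these patients, so even a short extra rating adds burden. The unblinding section also has routine unblinding after the treatment period, so the added rating might be made unblinded. Either defer routine unblinding until that rating is done, leaving emergency unblinding as it is, or report the rating separately from the blinded ones.
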